## 1 Protocol

### 1.1 Original protocol

#### HUMAN RESEARCH ETHICS COMMITTEE (HREC)

#### Effects of fast versus slow weight loss on fat, muscle & bone in postmenopausal women

#### PROTOCOL

#### OVERALL HYPOTHESES AND AIMS

The worldwide prevalence of obesity is increasing at an alarming rate and is a major risk factor for type 2 diabetes and other diseases. An important aspect of curbing the impact of the obesity epidemic is providing effective long-term treatments. In clinical practice, meal replacement programs such as very low energy diets (VLEDs) are used with increasing frequency. Although such programs are safe and effective in the short-term (up to one year), few studies have assessed their long-term safety and efficacy. While there is evidence that the ketosis associated with VLEDs attenuates the appetite stimulating effect of weight loss, the fact that weight loss, notably when induced by VLEDs, induces adaptive responses that would tend to inhibit loss of – and promote regain of – adiposity (particularly central adiposity) while decreasing lean body mass and muscle strength and compromising skeletal health is of concern. Such changes include decreases in metabolic rate and physical activity, and neuroendocrine alterations such as increased circulating concentrations of cortisol, decreased thyroid function and decreased circulating levels of insulin like growth factor-1. Because of the known deleterious effects of these changes on body composition, it is vital to assess whether VLEDs have negative effects that could ultimately increase the risk of conditions such as diabetes, cardiovascular disease, sarcopenia and osteoporosis. This question is of particular importance given that individuals may use VLEDs for several months at a time repeatedly over many years in order to manage their weight.

**The overall aim of this project is to compare the consequences of weight loss via VLED versus less severe energy restriction on the strength of adaptive responses to energy restriction, as well as effects on adiposity (particularly central adiposity and hepatic fat), lean body mass, muscle size, muscle strength and bone mass for up to 3 years.**

To this end, healthy obese postmenopausal women will be randomized to one of two weight loss interventions; one consisting of at least 12 months of lifestyle management with moderate energy restriction (~500 kcal deficit per day, ‘conventional diet’), and the other consisting of 3-5 months on a VLED followed by conventional diet or partial meal replacement for a total of at least 12 months.

## SPECIFIC HYPOTHESES AND AIMS

### Part 1: Effect of VLED versus conventional diet on parameters that affect body composition

**Hypothesis:** Whilst the ketogenic state induced by VLED abates some of the adaptive responses that can oppose weight loss, promote regain and impair body composition, VLED will nonetheless induce stronger overall adaptive responses to weight loss than conventional diet.

**Aim:** To compare the effects of VLED versus conventional diet in obese adults on appetite, physical activity, metabolic rate, neuroendocrine status, circulating gut hormone concentrations, markers of bone turnover and sympathetic reactivity up to 12 months after commencement of each intervention. Groups will be matched by the amount of weight or fat lost (at differing time points) as well as by duration of intervention (at different levels of weight or fat lost). We will also compare the magnitude of these parameters before and 1 week after transition from the ketogenic VLED to the non-ketogenic conventional diet, to determine the effect of ketosis on these responses.

### Part 2: Effect of VLED versus conventional diet on body composition

**Hypothesis:** While VLED will promote greater initial weight and fat losses than conventional diet, it may also promote greater losses of lean body mass, muscle diameter, muscle strength and bone density that may not be recovered, and a greater propensity for fat regain, particularly abdominally.

**Aim:** To compare the effects of VLED versus conventional diet in obese adults on body weight, waist and hip circumference, adiposity (including central adiposity and hepatic fat), lean body mass, muscle diameter, muscle strength and bone density for 36 months after the start of interventions.

## RESEARCH PLAN AND METHODOLOGY

**Participants.** This study will be performed in women because the estimated lifetime risk of osteoporotic fractures is 3-fold higher in women than in men (40% versus 13%). Additionally, while the prevalence of obesity is similar in both sexes, over 70% of the people presenting for treatment at the Metabolism & Obesity Services (Royal Prince Alfred Hospital) are women. One hundred (100) 45-65 year old women will be recruited, all of them sedentary (< 60 minutes physical activity / week) with class I or II obesity (30-40 kg.m^2). All women will be at least 5 years post-menopausal, to circumvent known effects of female sex hormone cycles and the menopausal transition on parameters under investigation. Eligibility for the study requires subjects to be euthyroid, non-diabetic, non-osteoporotic, non-smoking, ambulatory, weight stable for at least 6 months ( $\pm$  2 kg) and not taking medications known to affect heart rate, body composition or bone mass (e.g. glucocorticoids or beta blockers), no anti-resorptive therapy within the last 3 years, and no alcohol or drug dependency. Participants must not have metal in the body (e.g. from a pacemaker), as this is contraindicated for magnetic resonance imaging and

magnetic resonance spectroscopy. Respondents will be interviewed by telephone and if classified as eligible based on height, weight and medical history, will be invited to attend an information session.

**Participants will be randomised to VLED or conventional diet.** Both interventions will be administered at the Metabolism & Obesity Services and overseen by [name] and [name] and [name]. By having the interventions administered by actual clinical services rather than by our research laboratory, our findings will reflect effects of each diet as administered in the real world. We already know that both VLED and conventional diet result in average weight losses of approximately 20% and 12% of initial body weight after 12 months, respectively, and this study will demonstrate the effects of such real world clinical interventions on important parameters of long-term health and wellbeing, notably body composition and the factors that influence it.

The VLED consists of a 2,100 kJ (~500 kcal) per day program (Optifast®, Nestlé Nutritionals, Vevey, Switzerland), a high quality VLED with appropriate micronutrients that has been used extensively in the Metabolism & Obesity Services. Participants in the VLED arm will follow the VLED continuously for at least 3 months and for up to 5 months, or until a BMI of  $< 25 \text{ kg.m}^2$  is reached. As starting BMI is  $30\text{-}40 \text{ kg.m}^2$ , some volunteers on VLED may reach their target weight within 5 months. All volunteers on the VLED will then switch to either partial meal replacement for further weight loss if required (~1,500 kcal per day), or lifestyle intervention for weight maintenance. Meal replacements such as Optifast® are routinely used in this way, and many patients favour such ongoing usage. Two to three months on VLED is known to induce endocrine changes that have been shown in turn to adversely affect fat distribution, muscle function or bone density within 3 months as outlined above, and so using VLED for up to 5 months will be sufficient to reveal any effects on body composition, if present. The conventional diet is a lifestyle management program consisting of moderate kilojoule restriction (~500 kcal deficit per day) that has also been used extensively at the Metabolism & Obesity Services and published by [name]. Participants in both interventions will be advised to use pedometers and, after determination of baseline daily step counts, will be encouraged to gradually increase their physical activity in increments of 15 minutes per day of moderate physical activity such as walking (~1,500 steps per day).

**Sample size.** Our sample size of 100 women (50 on each diet) was selected based on the following power calculations and allowing for up to 20% attrition as we have seen in our previously published weight loss interventions. Most stringently, even if there is only a 5% difference between groups in – for example – fat free mass at any time point, we have the statistical power to detect it. Indeed, to detect a 5% difference in fat free mass (e.g. 50.3 versus 53.0 kg, and assuming a variance of 5 kg), the effect size is 0.52, so at 90% power and  $P < 0.05$ , it is necessary to study 39 women per group (50 – 50 x 20% attrition = 40). For other parameters under study, the samples sizes required to detect clinically meaningful differences between diets are smaller. For instance, based on studies in obese subjects that elicited a comparable weight loss to the 12-20% over 12 months that is expected in the current work, the effect size to detect differences between diets in the change in circulating thyroid hormone concentrations, bone mineral density and thigh muscle diameter are large ( $> 0.8$ ), indicating that a sample of 20 per group would provide 90% power to detect significant ( $P < 0.05$ ) differences between diets. From

previous studies we are not able to estimate potential differences between interventions for effects on appetite, but the effect size of energy deficit (and thus weight loss) on increasing appetite does appear to be dose-responsive ( $R=0.46$ ,  $P<0.001$ ). We can thus expect to detect a difference of moderate effect size for appetite with 30 participants per group. Based on comparable studies eliciting 12-20% weight loss in obese individuals, the effect size for differences between VLED & conventional diet with respect to changes in body weight, fat mass, waist circumference, visceral adiposity & resting metabolic rate in the first 3 months are very large ( $>1.1$ ), indicating that a sample of only 5 per group will provide 90% power to detect differences between the diets at  $P<0.05$ . At later time points, differences between diets with respect to body weight and parameters of body composition such as fat free mass will be smaller, but as described at the start of this section our sample of 50 participants on each diet provides sufficient power to detect this. We have access to gold-standard techniques to measure each of the outcome variables in this project, thereby minimizing variability and further contributing to our power to detect clinically meaningful differences between diets.

## **Part 1: Effect of VLED versus conventional diet on parameters that affect body composition**

**Rationale.** With the increasing use of VLEDs, it is important to compare the effects of ketogenic VLED and conventional diet directly on the adaptive responses to weight loss, since these parameters can significantly influence body composition and metabolic health. A suite of parameters will be investigated to identify possible mechanisms by which VLED and conventional diet may induce differential effects on body composition and muscle strength, thereby highlighting possible pathways for amelioration of any such differences. Additionally, these physiological responses will provide insights into reasons for lack of weight loss in some individuals.

**Weight stabilization.** At -0.5 months prior to commencement of the VLED or conventional diet as shown in the figure on the following page, volunteers will attend our clinical research facility for measurement of height (stretch stature), weight, waist and hip circumference and will then be instructed to maintain a steady weight ( $\pm 1$  kg) until the first time point (time = 0). This step reduces variability in baseline measures because dynamic fluctuations in energy balance significantly affect many of the outcome measures in this study. To achieve weight stability, volunteers will be given loan of a set of precise bathroom scales and instructions on how to maintain their weight with the aid of daily weighing.

[figure not shown]

**Time points and matching between groups.** At 0, 0.25, 1, 3, 6 and 12 months after commencement of each diet, the adaptive responses to weight loss summarized in the above figure (top box) will be assessed. The necessity of measuring these parameters at 6 different time points is twofold. Firstly, as the magnitude of adaptive responses to weight loss increases with the amount of weight lost, multiple time points will enable us to compare subjects on the VLED and conventional diet after a similar degree of weight or fat loss. For the purposes of matching and standardization of results, at each of these time points we will also measure weight, waist circumference, as well as fat mass and fat free mass using the 4-compartment model (without DXA) as described below and as previously published by [name]. Past experience from thousands of patients shows that weight losses after 0.25, 1 and 3 months on the VLED are similar to those induced by 1, 3 and 6-12 months on the conventional diet, respectively. In addition to matching for the degree of weight or fat loss, groups will also be compared at the same time points. A second reason for measuring these parameters at 6 time points is to determine the time of onset of various adaptive responses to weight loss, which will then be used to improve obesity interventions. For instance, we know that 2-3 months on a VLED induces strong adaptive responses that can promote weight regain and adverse body compositional changes. However, it is not known whether these responses are present for the entire duration of the VLED. If, for example, we discover that VLED (or conventional diet) induces changes such as increases in appetite and circulating cortisol levels or decreases in metabolic rate or serum IGF-1 that are seen only at the 3-month but not at the 1-month time point, then a future strategy might be to apply the intervention in intermittent bursts of less than 1 month, thereby attenuating the adaptive responses and their potentially deleterious effects on body composition.

**Effect of ketosis on parameters that affect body composition.** Participants in the VLED group will participate in this additional study. Following measurement of the adaptive responses to

weight loss at 3 months (at which point all participants will still be on the VLED, which results in ketosis due to its low carbohydrate and kilojoule content), participants will switch to a maintenance diet for 1 week followed by re-measurement at  $t = 3.25$  months. Fasting serum concentrations of ketones such as  $\beta$ -hydroxybutyrate will also be determined before and after this transition.

**Appetite.** Participants will be provided with a fixed (200 kcal) liquid meal (Optifast®, Nestlé Nutritionals, Vevey, Switzerland) at 9:00 am. Subjective measures of motivation to eat will be measured immediately before, after and at 1, 2 and 3 hours thereafter using the Electronic Appetite Rating System as described by [name].

**Physical activity.** Intensity and duration of daily physical activity will be measured using the Actigraph triaxial accelerometer worn on the waistband or on a belt. Accelerometry data will be collected during waking hours in the 7 days preceding each time point as previously described by [name]. Descriptive data will also be recorded in an activity diary, which will enable understanding of reasons for taking off the accelerometer (e.g. to swim or to sleep). Although all subjects will have the same standardized prescription to encourage physical activity, accelerometry and activity diary data combined with information from questionnaires (below) will provide insight as to possible effects of VLED or conventional diet on time spent exercising, in non-exercise activities or inactivity, and subjective measures of sleepiness.

**Resting metabolic rate** will be measured in the fasted state via indirect calorimetry using the TrueOne 2400 (Parvo Medics, Sandy, UT, USA) ventilated hood. Respired gases will be measured continuously for 30-min.  $VO_2$  and  $VCO_2$  will be converted to resting metabolic rate using the modified Weir equation as previously published by [name].

**Neuroendocrine status, circulating gut hormone and leptin concentrations** will be assessed by determining concentrations of the following analytes in serum or plasma from overnight-fasted subjects: free T3, free T4, reverse T3, TSH, ACTH, cortisol, luteinizing hormone, follicle stimulating hormone, progesterone, oestradiol, IGF-1, PYY, ghrelin and leptin. Analyses will be done at Royal Prince Alfred Hospital or in-house using commercial radioimmunoassay kits. Associate [name] has extensive experience in collection and interpretation of endocrine data with respect to energy homeostasis. As the hypothalamo-pituitary-thyroid, -adrenal, -gonadotropic and -somatotrophic axes (as well as gut hormone and leptin levels) are influenced by weight reduction and are known to powerfully influence body composition if sustained for several weeks, these serial measurements will demonstrate whether there is any differential effect of VLED versus conventional diet on the concentrations of hormones that could adversely affect body composition, as well as the duration of any such changes. A suite of hormones will be measured, as it will allow a more accurate assessment of whether the activity of each axis has been differentially altered by either diet.

**Bone.** The following parameters will be assessed to determine possible mechanisms by which VLED or conventional diet may induce any effects on bone mass, as previously published by Associate [name]: serum calcium, phosphate, albumin, alkaline phosphatase, vitamin D, parathyroid hormone, osteocalcin, procollagen type 1 N-propeptide, C-telopeptide of type-I collagen, urinary hydroxyproline and 24-hour urinary calcium. All of these will be

performed at Royal Prince Alfred Hospital or in-house.

**Sympathetic reactivity.** Deep inspiration induces vasoconstriction in skin capillaries via sympathetic activation, and dynamic weight loss has been shown to inhibit this response, possibly by the same hypothalamic alterations that induce the various adaptive responses to weight loss. Sympathetic reactivity will thus be assessed by inspiration-induced vasoconstriction, as determined by laser Doppler fluximetry (MoorVMS-LDF® Laser Doppler Blood Flow Monitor, Moor, England) as previously published. Because reduced sympathetic reactivity determined by this method predicts poor weight loss after bariatric surgery, and because this parameter is simple to measure and non-invasive, it may serve as a predictor of poor outcomes for weight loss or body composition in response to VLED or conventional diet. Such a measure could then be used in clinical practice to help identify individuals in likely need of more intensive support.

**Questionnaires.** Participants will complete validated instruments to assess quality of life (SF-36), depression symptoms (CES Depression Scale), Health Locus of Control (Multi-dimensional Health Locus of Control Questionnaire), sleep quality (Epworth Sleepiness Scale) & physical activity.

**Database maintenance and data analysis.** We have already developed a model database for use in our clinical research facility, and in collaboration with the NHMRC Clinical Trials Unit we are developing a database that can be used nationally. Database maintenance and data entry will be performed by [name] and will be directly overseen by Associate [name]. All data analyses will be performed using the SPSS statistical software package version 17.0 (SPSS Inc, Chicago, IL, USA). Repeated measures ANCOVA will be used for comparisons between all subjects on the VLED and the conventional diet, adjusting for confounding variables such as the amount of weight or fat lost or the length of time on the diet. Paired T-tests will be used to determine whether switching from the ketogenic VLED to the non-ketogenic maintenance diet alters the magnitude of any of the adaptive responses to weight loss.

**Outcomes Part 1:** This study will show for the first time whether VLED induces stronger adaptive responses to weight loss than conventional diet independent of the amount of weight or fat lost, and – by analysis with results in Part 2 – whether the magnitude of any of the adaptive responses predict outcomes for body composition and muscle diameter or strength. If so, then those adaptations could become targets for interventions to enhance weight loss and body composition in response to VLED or conventional diet. This work will also demonstrate whether ketones attenuate any of the adaptive responses to weight loss during VLED. If so, and if the magnitude of any adaptive responses predict outcomes for weight loss and body composition, then clinical interventions to ensure that patients on VLEDs maintain high circulating concentrations of ketones (e.g. by emphasizing the importance of compliance with the diet) could improve the effectiveness of VLEDs for the long-term management of overweight and obesity. An additional benefit of measuring multiple aspects of the adaptive response to weight loss at various time points is that it will enable subsequent improvements to both dietary interventions (e.g. by intermittent application of energy restriction), as well as early clinical identification of responders versus non-responders on both diets, thereby aiding the clinical management of obesity by targeting individuals with the greatest support needs.

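### The ketosis sub-study's paired test estimates the combined effect of ending the VLED; it does not isolate ketosis, as the Part 1 aim and outcomes claim

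*Supplement*

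**What the plan says.** All of this is in Supplement section 1.1 unless stated otherwise.

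- **Purpose.** The Part 1 aim compares the adaptive responses "before and 1 week after transition from the ketogenic VLED to the non-ketogenic conventional diet, to determine the effect of ketosis on these responses".
- **Before the switch.** "The VLED consists of a 2,100 kJ (~500 kcal) per day program". The protocol describes it as a diet "which results in ketosis due to its low carbohydrate and kilojoule content".
- **The switch.** Only the VLED group takes part. After the 3-month measurement, "participants will switch to a maintenance diet for 1 week followed by re-measurement" at 3.25 months, with ketones measured before and after.
- **Analysis.** "Paired T-tests will be used to determine whether switching from the ketogenic VLED to the non-ketogenic maintenance diet alters the magnitude" of the adaptive responses (Database maintenance and data analysis).
- **Conclusion to be drawn.** "This work will also demonstrate whether ketones attenuate any of the adaptive responses to weight loss during VLED" (Outcomes Part 1).
- **Energy balance.** Weight is stabilised before baseline because "dynamic fluctuations in energy balance significantly affect many of the outcome measures in this study" (Weight stabilization).

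Section 1.3.1 later fixes the VLED at 4 months and changes the ketone samples from serum to urine and whole blood. It lists no change to the design of this sub-study. The final analysis plan (section 2.2) does not mention the sub-study.

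**The concern.** The sub-study is meant to isolate ketosis, but the step that ends ketosis also ends most or all of a severe energy deficit. The protocol itself treats energy balance as a strong influence on these outcomes, strong enough to need control before baseline. It then changes energy balance sharply between the two measurements. No comparator group, no energy-matched non-ketogenic condition and no adjustment is described that could separate the two influences.

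What is at stake is the mechanistic conclusion. A null result could be reported as no effect of ketosis when two real effects have cancelled. A recovery caused by refeeding alone could be reported as evidence about ketosis.

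The documents also disagree on what the second diet is. The Part 1 aim calls it the conventional diet, defined elsewhere by a deficit of about 500 kcal/day. The sub-study description and the analysis paragraph call it a maintenance diet. The size of the energy change, and so the quantity being estimated, depends on which applies.

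**Working it through.** The documents give no sample size, power or effect size for this paired test, so there is no figure to reproduce. The check has three steps.

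**1. What differs between the two measurements**

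| | 3 months | 3.25 months |
|---|---|---|
| Energy intake | about 500 kcal/day | at expenditure (maintenance), or about 500 kcal/day below it (conventional) |
| Carbohydrate | low | higher (a non-ketogenic diet) |
| Ketosis | present | expected to have ended |
| Comparator over the week | none described | none described |

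Ketosis never changes while energy intake is held fixed, and energy intake never changes while ketosis is held fixed.

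**2. Size of the intake step**

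Let T be daily energy expenditure. The documents do not give it; 1,800 to 2,400 kcal is assumed.

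- Maintenance diet: step = T − 500, which is 1,300 to 1,900 kcal/day.
- Conventional diet: step = (T − 500) − 500, which is 800 to 1,400 kcal/day.
- Relative to the comparator arm's deficit of about 500 kcal/day: 800/500 = 1.6 up to 1,900/500 = 3.8.

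The documents alone support the order of size for the maintenance reading. Research plan and methodology gives partial meal replacement at about 1,500 kcal/day as a means of further weight loss. Maintenance should lie above that, so the step exceeds 1,500 − 500 = 1,000 kcal/day, or twice 500. This shows that the accompanying exposure is large. It does not measure the bias in any outcome.

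**3. What the paired test estimates**

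Let K be the change in a response caused by losing ketosis, and E the change caused by easing the energy deficit. Positive means the adaptive response gets stronger. Leaving aside carbohydrate, time and repeat-measurement effects:

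expected paired difference = K + E

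One mean difference cannot yield both terms. To illustrate the consequence, take 40 pairs (50 less 20% attrition, from Sample size) and a two-sided 5% test. Assume values of K and E in SDs of the paired difference. The noncentrality is (K + E)√40; for example 0.5 × 6.32 = 3.16.

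| K | E | K + E | P(significant, response stronger) | P(significant, response weaker) |
|---|---|---|---|---|
| 0.5 | 0 | 0.5 | 0.87 | 0.00 |
| 0.5 | −0.25 | 0.25 | 0.34 | 0.00 |
| 0.5 | −0.5 | 0 | 0.025 | 0.025 |
| 0.5 | −0.75 | −0.25 | 0.00 | 0.34 |
| 0.5 | −1.0 | −0.5 | 0.00 | 0.87 |
| 0 | −0.25 | −0.25 | 0.00 | 0.34 |
| 0 | −0.5 | −0.5 | 0.00 | 0.87 |

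The rows K = 0.5, E = −1.0 and K = 0, E = −0.5 have the same expected result, so the test cannot tell a real ketosis effect from none.

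Opposing signs follow from the protocol's own premises for appetite. The overall aims say ketosis blunts the rise in appetite with weight loss; Sample size says energy deficit raises appetite in a dose-related way. The Part 1 hypothesis also expects stronger responses overall on the VLED even though ketosis abates some of them. That makes |E| > |K| plausible for some outcomes but does not establish it for a one-week change.

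**The case against.** **The test itself is worded correctly.** The analysis paragraph says it examines the effect of switching diets, which a paired comparison can address, apart from time and repeat-measurement effects. This stands. The fault lies in the aim and in Outcomes Part 1, where the result is credited to ketosis or ketones.

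**The text may not be current.** The final protocol is only linked. With the VLED fixed at 4 months and the final analysis visits at 0, 4, 6 and 12 months (plus 0.25 and 1 month for some measures), the 3 and 3.25 month schedule may have moved. This also stands and limits confidence. The listed changes neither remove nor redesign the sub-study, and the problem does not depend on the month.

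**A reader might infer that the contrast says nothing about ketosis.** The documents do not support that. Where easing the deficit should weaken a response, it works against the hypothesis. If appetite rose although women were eating more, relief of the deficit could not readily explain it. Such a result would be suggestive, though not proof, because carbohydrate intake and time also change. A null is what cannot be interpreted.

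**A reader might also infer that a refeeding rebound would produce false advice to keep ketones high.** The direction is wrong. Recovery of thyroid hormones, metabolic rate or IGF-1 after ketosis ends would count against the idea that ketones attenuate these responses. Outcomes Part 1 also makes the clinical step conditional on attenuation being shown and on the responses predicting outcomes. The likelier error is a missed or reversed ketosis effect.

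**The intake comparison has limits.** It sets a one-week step against a deficit sustained for at least 12 months, so it shows the scale of the exposure and not of any bias.

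**Conclusion.** The point holds for the protocol text shown. The paired test estimates the combined effect of ending the VLED, and the ketosis-specific claims in the Part 1 aim and in Outcomes Part 1 go beyond it. That conclusion needs no numerical assumption.

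The intake step of 800 to 1,900 kcal/day rests on the assumed expenditure. The probabilities rest on assumed K and E with 40 pairs. They show that masking, sign reversal and misattribution can occur, not that they will. Which occurs depends on each outcome's two component effects, which the documents do not give.

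The effect is confined to a secondary mechanistic question. The primary outcome, whole-body lean mass at 12 months, is not affected. A repair in the linked final protocol cannot be excluded.

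**What to change.** 1. Reconcile the Part 1 aim with the sub-study description and the analysis paragraph on which diet follows the VLED. Reconcile the 3 and 3.25 month timing with the 4-month VLED in section 1.3.1.
2. Restate the Part 1 aim and the Outcomes Part 1 conclusion as the effect of ending the VLED, with ketosis and energy restriction combined. Draw no ketone-specific conclusion from the paired test. State that a null does not show that ketosis has no effect.
3. If change in response is also regressed on change in ketones, label the analysis exploratory and still confounded. The protocol ties ketosis to energy as well as carbohydrate content, so a woman's fall in ketones also tracks her rise in intake and her adherence. Do not use absence of a dose-response as a decision rule: a threshold effect, or little variation in ketone change between women, would hide a true effect. If one-week weight change is to be a covariate, confirm that weight is recorded at the second visit, which the listed weight time points do not include.

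Steps 1 and 2 are wording changes with no new visits or measurements; step 3 is optional. The price is a weaker mechanistic claim about ketosis.
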